### Planned analyses

All analyses will be carried out according to the intention-to-treat rule consistent with standard practice in most trials. The primary aim of this study is to assess the impact of the intervention on sales of healthy children’s menu items. The primary dependent variables (gross sales in dollars and units) are continuous measures that are normally distributed or may be transformed to approximate normality by natural log or the Box-Cox transformation. Thus, normal-based models will be emphasized, with care taken to assess this assumption and, if necessary, apply appropriate transformations. Based on bivariate analyses (independent sample *t*-test and chi-square test), significant differences between the two intervention conditions will be included in the subsequent multivariate mixed model analysis for covariance adjustment.

For the primary aim of assessing the effectiveness of the interventions on sales of healthy children’s menu items, we will use mixed effects models. The primary predictor, intervention condition assignment, along with sales over time between the two intervention conditions will be placed in the fixed effect part of the models. These covariates will be adjusted for their influence on the intervention effect. The restaurant ID will be placed in the random effect part of the model to adjust for the clustering effects. The proposed multilevel models will be fitted using SAS PROC MIXED or PROC GLIMMIX when examining non-normal variables such as a dichotomous outcome.

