## Methods/Design

### Overview and study design

Consistent with CONSORT guidelines [24], KCRP is a cluster randomized trial with eight pair-matched independent restaurants randomized to a menu-only versus a menu-plus intervention condition. Outcome and impact evaluation activities are designed to determine whether the interventions result in sales of healthy children’s menu items and changes in ordering behavior among dining parties with children. Weekly sales data are collected from restaurant managers/owners for 18 weeks, including 4 weeks pre-intervention (baseline). Unobtrusive observations are attempted with approximately five dining parties with children every other week for 18 weeks in each restaurant to capture ordering behavior. Post-order and post-meal interviews with these same dining parties, as well as some unobserved dining parties, capture reported ordering and consumption behaviors. An extensive process evaluation protocol, including ongoing documentation by KCRP intervention staff, restaurant audits and manager/owner interviews, assesses key dimensions of implementation [25], including dose delivered, dose received, and intervention fidelity. Employees are recruited to participate in the restaurant training; however, the only evaluation activity they are involved in is assessment of the training. This study was conducted according to the guidelines laid down in the Declaration of Helsinki and all procedures involving human participants were approved by the Institutional Review Board of San Diego State University.

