**Fig. 1 Fig1:**
[figure not shown]
Study design

Initial restaurant recruitment strategies involved a phone call or drop-in visit to schedule an in-person meeting with the restaurant manager/owner. If restaurant employees informed the KCRP recruiter that the restaurant manager/owner should be contacted first via email, an email with the introductory letter was sent. During the recruitment meeting with the manager/owner, the KCRP recruiter reviewed study requirements and gave the manager/owner a study fact sheet with testimonials from managers/owners who participated in the pilot study and answers to frequently-asked questions. In addition to learning more about the study, the manager/owner was told his/her restaurant would receive $300 for participating, the manager/owner would receive $20 for each of two interviews completed, and wait staff and customers would receive $10 per shift and $5, respectively, the former for allowing KCRP evaluation staff to shadow the wait staff and the latter for completing the interviews. If the manager/owner was interested, the KCRP recruiter completed eligibility screeners for both the restaurant and the manager/owner. If eligibility was met and the manager/owner agreed, the two parties signed a letter of agreement and confidential disclosure agreement. The manager/owner also signed an informed consent form for the interviews. Restaurants were pair-matched on availability of a children’s menu (yes or no) and with one exception, on size (small-to-medium or medium-to-large based on number of tables). The exception involved one set of pair-matched restaurants both without a child menu but of different sizes. Once a pair was identified, the project biostatistician randomly assigned each restaurant to either the menu-only or menu-plus intervention condition and the intervention planning and development phase for the pair commenced. KCRP evaluation staff blinded to intervention condition assignment completed baseline measures.

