#### Primary outcome evaluation

Sales in gross dollars and units sold are tracked for existing and new children’s menu items, as well as total gross food and beverage sales per week excluding alcohol. Weekly detailed sales data are collected for an 18-week period, starting during the 4-week baseline period. Managers/owners are given a sales data guide to help them prepare the data to maximize its utility for the study. In addition, reminder emails/phone calls are used to maximize getting the data in paper or electronic form. These data have the potential to yield information on calories sold in the form of new children’s menu items; however, funding limits prohibit us from evaluating the nutritional quality of existing children’s menu items.

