### Baseline characteristics

Depicted in Table 2 are manager/owner and restaurant characteristics at baseline. Restaurant managers/owners are mostly male (88 %) and all had some college education. Average years managing the restaurant are 12 (SD = 8) and the managers/owners reported working, on average, over nine hours a day (SD = 2). As desired, the eight restaurants are all independent, with two of the owners having a partnership in two other restaurants. One matched pair did not have a children’s menu at baseline; the remaining six restaurants did. The average number of full-time employees is 13 (SD = 7), average number of tables is 33 (SD = 7), and 75 % typically have 60 or more dining parties on a busy night. Average weekly sales are $21,500 (range = $8000 to $60,000).

**Table 2 Tab2:** Manager/owner and restaurant characteristics (*N* = 8)

	%, Mean, or median	N, SD, or range
Manager/Owner characteristics		
Mean age in years	50.6	12.2
Male	87.5 %	7.0
White/Caucasian	71.4 %	5.0
Some college	100.0 %	8.0
Mean years managing this restaurant	12.2	8.0
Mean hours worked in a typical day	9.4	2.3
Restaurant characteristics		
Mean years in operation	17.8	15.2
Mean number of full-time employees	12.9	6.6
Mean number of part-time employees	11.1	11.5
Mean number of tables	33.0	7.2
Parties on busiest night of the week		
50-59 parties	25.0 %	2
60-69 parties	37.5 %	3
70+ parties	37.5 %	3
Children’s menu available	75.0 %	6
Restaurant marketing in English only	87.5 %	7
Median weekly sales	$21,500	$8000–$60,000

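### The plan gives restaurant size no stated role in the primary analysis of absolute sales, although size spans $8000 to $60,000 a week and total sales are collected; a prespecified baseline-sales covariate would protect precision

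*Protocol article*

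**What the plan says.** The design is "eight pair-matched independent restaurants randomized to a menu-only versus a menu-plus intervention condition" (Overview and study design), so four restaurants per condition. Planned analyses sets the outcome scale: "The primary dependent variables (gross sales in dollars and units) are continuous measures". The model there has condition and sales over time as fixed effects and restaurant as a random effect. A log or Box-Cox transformation is available to reach normality. Covariates enter if they differ significantly between conditions in bivariate tests.

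Primary outcome evaluation says that the sales of children's items are tracked, "as well as total gross food and beverage sales per week excluding alcohol". It adds: "Weekly detailed sales data are collected for an 18-week period, starting during the 4-week baseline period". Planned analyses assigns total sales no role.

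Baseline characteristics reports the spread in size: "Average weekly sales are $21,500 (range = $8000 to $60,000". (Table 2 calls the $21,500 a median. The two should be reconciled, but the figure is not used below.)

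The section on restaurant selection and condition assignment says that pairs were matched on having a children's menu and, with one exception, "on size (small-to-medium or medium-to-large based on number of tables". The exception is a pair without a children's menu.

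**The concern.** If sales of healthy children's items rise with a restaurant's overall business, much of the spread between restaurants in absolute sales reflects size and not response to the intervention. With four restaurants per arm, that spread goes straight into the standard error of the comparison, and one large restaurant can tilt the arm means by chance.

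The safeguards in the plan deal with this only in part:

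- **Baseline change.** The new items have no sales before launch, and existing items cannot stand in for them because "funding limits prohibit us from evaluating the nutritional quality of existing" children's items. Subtracting baseline therefore does not remove size.
- **Random restaurant effect.** It represents size as between-restaurant variance. It does not take size out of the contrast between arms.
- **Log transformation.** It makes effects multiplicative and damps the pull of the largest restaurant, but size variance stays on the log scale.
- **Matching.** It used two table-count classes, failed on size in one of four pairs, and no pair term is named in the model.
- **Covariate screen.** It is the only stated route for total sales into the model, and it has little power at four against four.

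At stake is precision, and exposure to chance imbalance in size. Randomisation still protects against systematic bias.

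**Working it through.** The article gives no power calculation, effect size or outcome variance, so there is no design figure to reproduce.

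**Inputs from the article.** Range of weekly sales $8000 to $60,000; 8 restaurants, 4 v 4; tables mean 33.0, SD 7.2 (Table 2); one of four pairs mismatched on size.

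**Assumptions, not in the article.** Sales are log-normal across restaurants. The log of healthy-item sales has slope b on log total sales. The remaining between-restaurant log SD is s, taken as 0.3 with a range of 0.2 to 0.5. Two-sided alpha is 0.05. Pairing is ignored except where stated.

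**1. Spread of size.** 60,000/8000 = 7.5. The expected range of eight normal values is 2.847 SD, so log SD = ln(7.5)/2.847 = 0.708 and the log variance is 0.501.

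**2. What matching can do.** The coefficient of variation of tables is 7.2/33.0 = 0.22. If sales were proportional to tables, perfect table matching would remove about 0.218²/0.708² = 0.095, or 10%, of the size variance. Pairing may capture more by other routes, so step 4 also shows 50%.

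**3. The significance screen.** The SE of a 4 v 4 difference in mean log sales is 0.708 × sqrt(2/4) = 0.50. Significance on 6 df (t = 2.447) needs an observed ratio of geometric means of exp(2.447 × 0.50) = 3.4. If the underlying ratio were 2, the chance of flagging it is 22% (noncentral t, 6 df).

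**4. SE of the log ratio between arms at b = 1.**

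- Unadjusted: sqrt(2/4 × (0.501 + s²)).
- Unadjusted, matching removes half the size variance: sqrt(2/4 × (0.251 + s²)).
- Fixed offset: sqrt(2/4 × s²).
- Covariate: the offset SE at b = 1 times sqrt(1 + 1/(8 − 4)) = sqrt(1.25), the average penalty for estimating the slope with a normal covariate at 4 v 4.

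| s | Unadjusted | Half removed by matching | Offset | Covariate |
|---|---|---|---|---|
| 0.2 | 0.52 | 0.38 | 0.14 | 0.16 |
| 0.3 | 0.54 | 0.41 | 0.21 | 0.24 |
| 0.5 | 0.61 | 0.50 | 0.35 | 0.40 |

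At s = 0.3 the 95% interval extends by a factor of exp(2.447 × 0.544) = 3.8 unadjusted, exp(2.447 × 0.413) = 2.7 with half removed, exp(2.447 × 0.212) = 1.7 with the offset (all 6 df), and exp(2.571 × 0.237) = 1.8 with the covariate (5 df).

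**5. If item sales track total sales less closely (s = 0.3, pairing ignored).** The size variance is b² × 0.501 unadjusted and (1 − b)² × 0.501 with an offset. The covariate estimates b, so its SE does not depend on b.

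| b | Unadjusted | Offset | Covariate |
|---|---|---|---|
| 1 | 0.54 | 0.21 | 0.24 |
| 0.5 | 0.33 | 0.33 | 0.24 |
| 0.3 | 0.26 | 0.41 | 0.24 |
| 0 | 0.21 | 0.54 | 0.24 |

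The offset helps only when b exceeds 0.5. At b = 0.3 it raises the SE from 0.26 to 0.41. The covariate's worst case is b = 0, where it costs 0.24 against 0.21.

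**The case against.** Total sales are listed under the primary outcome, and the unseen analysis plan may give them a role. That stands to this extent: the fair statement is that no use is stated, not that the data go unused. But the article does fix how covariates enter, and that rule is the weak one.

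Proportionality is an assumption. Nothing in the article shows that children's items follow dollar sales. Table 2 suggests that customer volume varies less than revenue: busiest-night parties are 50–59 in two restaurants, 60–69 in three and 70 or more in three, though the top class is open-ended. The $8000 to $60,000 range is also not said to exclude alcohol, so 0.708 may not describe the collected non-alcohol totals. Both points stand. They make the gain uncertain and rule out a fixed offset as the safe choice.

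Matching lowers the true variance of the contrast even if no pair term is fitted. This stands too: at s = 0.3 and b = 1, removing half the size variance cuts the gain from a covariate from 2.3-fold (0.544/0.237) to 1.7-fold (0.413/0.237), if the covariate SE is taken as unchanged.

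A reader might infer that size swamps any intervention effect, that the arm holding the largest restaurant will tend to win, or that absolute sales is the wrong outcome. The documents support none of these. They give no effect size or variance for healthy-item sales, 7.5 compares only the two extremes, and the stated aim is the impact on sales, for which absolute sales under randomisation is a legitimate target.

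**Conclusion.** The concern holds as one of precision and chance imbalance. The plan has a strong candidate covariate in hand but admits it only through a test that would usually miss a two-fold size difference between arms.

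With full proportionality and residual log SD 0.3, a prespecified covariate lowers the standard error from about 0.54, or 0.41 if matching already removes half the size variance, to about 0.24. With a slope of 0.3 the gain is slight (0.26 to 0.24), and with no relation there is a small loss (0.21 to 0.24). These figures rest on a log SD inferred from a range, log-normal sales and an assumed residual SD.

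The change is worth making because the possible gain is large, the possible loss small and the data already requested. It does not cure the limits of having only four restaurants per arm.

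**What to change.** In Planned analyses, replace the significance screen for this one variable with a prespecified covariate: the log of each restaurant's mean weekly non-alcohol sales over the 4 baseline weeks, in the log-scale model of new children's item sales. Do not impose it as a fixed offset.

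Use baseline and not concurrent totals. The menu-plus banners are meant to draw in families, so concurrent totals may themselves be changed by the intervention.

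Keep absolute dollars and units as the reported outcomes, and show units per $1000 of sales as a sensitivity analysis.

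The cost is a sentence or two of wording and one restaurant-level degree of freedom (5 in place of 6 in the calculation above). No new data are needed.

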## Discussion

From among the 92 potentially eligible restaurants, 32 were ineligible prior to approaching the manager/owner for not being a full-service restaurant, having too few tables, or not having the capability to provide sales data. From the remaining 57 restaurants, 10 never responded to any recruitment attempts and six were never approached due to completion of recruitment. Forty-one restaurants were approached in-person for participation; nine were ineligible, 18 refused to participate, six never provided a final decision, and eight agreed (see Fig. 1). Among the reasons given for participating, managers/owners noted that they were interested in providing healthier items for children. Among reasons for refusing, managers/owners said they were too busy or not interested, their restaurants were undergoing major changes during the upcoming months, or the timing of the study necessitated more extensive management involvement than they could provide during the peak tourist season. However, other managers/owners reported they were not interested in “telling customers how to eat” or did not want to change their existing menus.

Restaurants are pair-matched at recruitment to ensure equivalency across characteristics randomized to intervention conditions (e.g., presence of a children’s menu). Thus, once a restaurant is recruited, a second restaurant from the list is recruited with similar characteristics. One restaurant is randomly assigned to the menu-only intervention condition and the other to the menu-plus intervention condition. Baseline assessments take place during the 4 weeks prior to the introduction of the new children’s menus and are conducted by KCRP evaluation staff blind to treatment condition.

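### Choosing primary-model covariates by between-condition significance tests is uninformative with four restaurants per arm: it misses large chance imbalances and leaves the model unknown until the data are seen

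*Protocol article*

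**What the plan says.** Overview and study design sets the size: "KCRP is a cluster randomized trial with eight pair-matched independent restaurants randomized to a menu-only versus a menu-plus intervention condition". The Discussion confirms the split within each pair: "One restaurant is randomly assigned to the menu-only intervention condition and the other to the menu-plus intervention condition". The comparison is therefore four restaurants against four.

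Planned analyses fixes how covariates reach the primary model. The rule opens "Based on bivariate analyses (independent sample", names the t-test and the chi-square test, and concludes that "significant differences between the two intervention conditions will be included in the subsequent multivariate mixed model analysis for covariance adjustment". The next paragraph, on the primary mixed model, adds "These covariates will be adjusted for their influence on the intervention effect". Clustering is handled by a random effect: "The restaurant ID will be placed in the random effect part of the model".

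The section gives no second route for a covariate to enter. It does not state the significance level, or whether the tests are run on restaurants, restaurant-weeks or dining parties.

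**The concern.** After randomisation, a test between arms asks whether chance produced a difference, which is already known. It does not ask whether the variable predicts sales, which is what matters for adjustment. With four restaurants per arm it is also a poor detector of imbalance.

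Three things follow:

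- A prognostic variable can be badly out of balance and stay out of the model.
- A variable unrelated to sales can enter by chance and use up one of the six between-restaurant degrees of freedom.
- Nobody can write down the primary model until the data have been examined.

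The rule also fits badly with the matched design. The article reports one matched pair without a children's menu and six restaurants with one, so that factor stands at 3/4 v 3/4. It can never test as different and can never enter by this route. The tests named are for independent samples and ignore the pairs.

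**Working it through.** The article gives no power, alpha or threshold for this step, so there is no planned figure to reproduce. The check is of how the stated rule behaves.

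**Inputs.** Four restaurants per arm (Overview and study design; Discussion). Weekly sales from $8000 to $60,000 (Baseline characteristics, Table 2). Assumed: tests run on restaurants, two-sided 0.05.

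**1. Smallest difference the t-test can flag.** With 4 + 4 − 2 = 6 df, the critical t is 2.447. The observed difference must reach 2.447 × √(2/4) = 2.447 × 0.707 = 1.73 within-arm SD. At alpha 0.10 the threshold is 1.943 × 0.707 = 1.37 SD, and at 0.20 it is 1.440 × 0.707 = 1.02 SD.

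**2. Chance imbalance that goes unflagged.** Under simple 4 v 4 randomisation, a given normal covariate differs between arms by at least 1 SD about 16% of the time (simulation). The test flags about 27% of those cases.

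**3. Chi-square.** With four per arm, the expected count in a cell is half the column total, and the two cells of that row sum to 4. No expected count can therefore exceed 4.

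| Split | Pearson p | Fisher p |
|---|---|---|
| 3/4 v 1/4 | 0.157 | 0.486 |
| 4/4 v 2/4 | 0.102 | 0.429 |
| 4/4 v 1/4 | 0.028 | 0.143 |
| 4/4 v 0/4 | 0.005 | 0.029 |

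In the third row, whether the covariate enters depends on an approximation that the exact test does not support.

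**4. Entry by chance.** If k independent covariates are each tested at 0.05, the chance that at least one enters is 1 − 0.95^k. This is 23% for k = 5 and 40% for k = 10.

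**5. Illustration with weekly sales.** Assume log-normal sales and ignore the matching. The log range is ln(60,000/8000) = 2.015, and the expected range of eight normal values is 2.847 SD, so the log SD is about 2.015/2.847 = 0.708. The difference in arm means then has SD 0.708 × 0.707 = 0.500. The chance that it exceeds ln 1.5 = 0.405 in either direction is about 42%. By simulation, the t-test flags about 12% of those cases. At this SD, a gap of up to exp(1.73 × 0.708), about 3.4-fold, can go unflagged.

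**6. Consequence for the estimate.** This is a restaurant-level simulation with no intervention effect and one covariate with correlation rho to the outcome (rho is assumed). Errors and SDs are in outcome SD; the second and third result rows are conditional on the covariate favouring one arm by at least 1 SD.

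| | rho 0.5 | rho 0.8 | rho 0.9 |
|---|---|---|---|
| Overall type I error, rule | 4.8% | 3.6% | 2.8% |
| Mean error given imbalance, rule | 0.46 | 0.73 | 0.81 |
| Mean error given imbalance, prespecified | 0.03 | −0.03 | −0.01 |
| SD of estimate, rule | 0.73 | 0.67 | 0.65 |
| SD of estimate, prespecified | 0.70 | 0.48 | 0.34 |

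Given that imbalance, rejection under the null is 7% to 10% with the rule and about 5% with prespecified adjustment.

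**7. Price of one fixed covariate.** Degrees of freedom fall from 6 to 5 and the critical t rises from 2.447 to 2.571. If the covariate is balanced, interval width breaks even when residual variance falls by 1 − (2.447/2.571)² = 9%. Imbalance raises the break-even point. The variance of the adjusted effect carries a factor 1 + t²/6, where t is the covariate's own between-arm statistic. With 6 df the mean of t² is 6/4 = 1.5, so the factor averages 1.25 and the break-even point averages 1 − 0.906/1.25, about 28%.

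Adding fixed pair effects as well leaves 8 − 1 − 1 − 3 − 1 = 2 df and a critical t of 4.303. Residual variance would then have to fall by 1 − (2.447/4.303)² = 68% even with a balanced covariate.

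**The case against.** **Error rate.** A reader might infer that the rule breaks the trial's type I error rate. The documents do not support that. The article states no alpha for the rule to violate, and the overall rejection rate in the simulation was about 3% to 5%. The rise to 7% to 10% is conditional on a large imbalance and on assumed correlations.

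**Unit of testing.** A reader might also take 4 v 4 as the stated unit. It is not stated. The same section opens by covering all analyses, and 45 observations or interviews per restaurant are planned. Tests on restaurant-weeks or parties as if independent would have a different fault, because they would ignore clustering.

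**Matching and the sales figures.** Restaurants were matched on children's menu and, with one exception, on size by number of tables. If table count tracks sales, 42% is too high. The log-normal shape and the SD inferred from a range are assumptions. The article gives no figure for how strongly total sales predict sales of healthy children's items.

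**Baseline weeks in the model.** Sales over time enter the fixed part of the model and four weeks precede launch, so stable differences between restaurants partly cancel for items already on sale. This is fair, but items first sold at launch have no baseline sales against which to cancel.

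**A condensed article.** The absence of a covariate list is not a fault in an article, and none is claimed here. The point concerns a selection rule that the article does state. Nor does Table 2 show the fault: it reports "manager/owner and restaurant characteristics" pooled over all eight restaurants, with no comparison by arm and no p-values.

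These objections limit the size and wording of the point. They do not rescue the rule as a way of choosing covariates.

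**Conclusion.** The point holds in a limited form. The article selects covariates for the primary model by significance between arms. At restaurant level that screen needs an observed difference of 1.73 SD at the 0.05 level, and it relies on a chi-square approximation that fails at this size. A looser level lowers the threshold but does not make the screen a test of prognostic value: at 0.20 it is still 1.02 SD.

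The consequence is bias conditional on a missed imbalance, loss of precision when a strong predictor is left out, and a primary model that is not fixed in advance. The threshold and the p-values are exact, given restaurant-level testing and a two-sided 0.05 level. The sales figures of 42% and 12% are an illustration only, and the simulated errors depend on the assumed correlations. This should be changed, but it does not by itself invalidate the trial.

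**What to change.** Delete the bivariate-test rule. Before outcomes are seen, name one prognostic baseline covariate for the primary model: the log of mean weekly total food and beverage sales, excluding alcohol, over the four baseline weeks. Primary outcome evaluation already plans to collect these data, so no new data or budget are needed. State that this covariate enters whatever its balance between arms, and that no other covariate is added on the strength of a test.

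The cost is one between-restaurant degree of freedom (6 to 5, critical t 2.45 to 2.57). It is recovered if the covariate explains about 9% or more of between-restaurant variance when it is balanced, and a larger share when it is not.

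Do not require fixed pair effects on top of this covariate, because about 2 df would remain. Whether and how to model the pairs is a separate choice, also to be made in advance.

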### Evaluation

#### Overview

A mixed-methods approach is used to evaluate the intervention on sales of healthy children’s menu items over an 18-week period, including during the 4-week baseline period. Primary outcomes are gross sales of healthy children’s menu items and units sold. Observations and interviews with a convenience sample of dining parties with children below the age of 18 years will determine changes in ordering behavior. Manager/owner interviews conducted during the baseline period and during the final 4 weeks of the 18-week data collection period (herein referred to as post-intervention period), and restaurant audits at baseline, mid-point of intervention and post-intervention periods will provide evidence of intervention impact on the manager/owner and restaurant environment. Our process evaluation includes an additional manager/owner interview once intervention activities are completed (i.e., exit interview). KCRP intervention staff visit the restaurants to capture implementation, dose delivered, dose received, and fidelity, and manager/owner and customer satisfaction with the intervention (see Table 1).

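### Restaurant ID is the only random term named in the primary model; read as a random intercept, it does not protect the condition-by-time contrast from variation among the 8 restaurants

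*Protocol article*

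**What the plan says.** Under Overview and study design, the protocol article describes the design: "KCRP is a cluster randomized trial with eight pair-matched independent restaurants randomized to a menu-only versus a menu-plus intervention condition". Weekly sales are collected for 18 weeks, the first 4 of them baseline. Under Evaluation, Overview: "Primary outcomes are gross sales of healthy children’s menu items and units sold".

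The Planned analyses section specifies mixed effects models for the primary aim. The fixed part is described as "intervention condition assignment, along with sales over time between the two intervention conditions will be placed in the fixed effect part of the models". For the random part: "The restaurant ID will be placed in the random effect part of the model to adjust for the clustering effects". The software sentence reads: "The proposed multilevel models will be fitted using SAS PROC MIXED or PROC GLIMMIX when examining non-normal variables such as a dichotomous outcome".

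Restaurant ID is the only random term named, and it is presented as the adjustment for clustering. The article gives no time coding, residual covariance, degrees-of-freedom method, alpha or variance components.

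**The concern.** With condition and sales over time by condition in the fixed part, the intervention effect is most naturally carried by the condition-by-time term: do sales move differently in the two conditions after launch? A random intercept absorbs constant differences in level between restaurants. It does not allow restaurants to differ in how much they change, so it gives the condition-by-time term no between-restaurant error.

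The design gives reasons to expect differing changes. The Baseline characteristics section reports weekly sales from $8,000 to $60,000 and two of the eight restaurants without a children's menu. Under Intervention conditions, removal of existing items is optional, substitutions are possible, and menu-plus items are chosen restaurant by restaurant.

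At stake are the standard error, confidence interval and p-value for the primary aim. A chance difference in uptake between two groups of four restaurants could be read as an intervention effect.

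**Working it through.** The article states no power, alpha or df figure, so there is nothing to reproduce. Two-sided alpha 0.05 is assumed.

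**Inputs from the protocol article.** 8 restaurants, 4 per condition in 4 pairs; 18 weekly values each, 4 baseline and 14 later; restaurant ID as the random term.

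**Residual df.** Observations: 8 × 18 = 144. With pre/post or linear time, the 8 restaurant intercepts plus time and condition-by-time take 10 (condition lies within the intercepts): 144 − 10 = 134. Three phases give 132. Categorical weeks take 8 + 17 + 17 = 42, leaving 102. A test on one value per restaurant has 8 − 2 = 6 df, or 4 − 1 = 3 df within pairs. Critical t values are 1.98 (134 df), 2.45 (6 df) and 3.18 (3 df).

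**Why the intercept drops out.** Let σ be the weekly residual SD and τ the SD of the true restaurant-specific change. A restaurant's post-minus-pre difference removes its intercept. With independent weeks the variance of that difference is τ² + σ²(1/4 + 1/14) = τ² + 0.3214σ². The random-intercept model uses only the second term, with σ² estimated from the pooled weekly residual.

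**Hand check, pre/post coding, independent weeks, σ = 1.**
- The true variance exceeds the residual part by the factor 1 + τ²/0.3214 = 1 + 3.111τ².
- The pooled residual absorbs a little of this: its expectation is 1 + 6 × 3.111τ²/134.
- τ = 0.5: 1.778/1.035 = 1.718, square root 1.311. The nominal cut-off of 1.978 acts like 1.978/1.311 = 1.51, a normal-approximation error rate of about 13%.
- τ = 1: 4.111/1.139 = 3.609, square root 1.900. The cut-off acts like 1.04, an error rate of about 30%.

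**Simulation under no condition effect** (20,000 runs per setting; in balanced data the random-intercept test of this term is the within-restaurant least-squares test). τ/σ and the week-to-week AR(1) correlation are assumptions. The first four rows use an ordinary baseline.

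| Setting | τ/σ = 0 | 0.5 | 1.0 |
|---|---|---|---|
| Pre/post, independent weeks | 4.8% | 13.4% | 29.7% |
| Pre/post, AR(1) 0.3 | 12.8% | 19.6% | 34.2% |
| Linear time, independent weeks | 4.7% | 9.7% | 20.2% |
| Linear time, AR(1) 0.3 | 13.4% | 18.2% | 28.4% |
| Pre/post, AR(1) 0.3, all baselines zero | under 3% | about 11% | about 32% |

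At τ/σ = 2 with pre/post coding and an ordinary baseline the rate is 50-52%. In the zero-baseline setting it is also under 3% at τ/σ = 0.25, because the four constant weeks shrink the pooled residual less than they shrink the true variance of the change.

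**Restaurant-level comparator.** With an ordinary baseline, a t-test on one change or slope per restaurant held about 4.6-5.4% in every setting, on 6 df unpaired or 3 df paired.

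**The case against.** A reader might infer that the plan commits to a random intercept and nothing else, and that its false-positive rate is several times nominal as a matter of fact. The documents do not support either statement.

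- The article says neither intercept nor only. It does not exclude a random slope or residual correlation, and a fuller analysis plan could add them. This stands. What remains is that the article names one term and assigns it the job of handling clustering; on its ordinary reading, that term does not do the job for condition-by-time.
- The 134 df is not in the article. It depends on time coding and on a residual-type df method. This also stands, but 102 df is equally far from 6 or 3.
- Without variance components the inflation is not established. It vanishes when restaurants share the same change and weeks are independent. It can reverse if measured sales are zero everywhere at baseline, which is plausible because the items are new and existing items are not nutritionally evaluated. This stands, and it makes the size conditional.
- The article calls condition assignment the primary predictor. A condition main effect with a restaurant intercept is judged against variation among restaurants. Even on residual df, its error would be only about 9-10% (a 6-df t against a cut-off of 1.98). This limits the point to the condition-by-time term. That term remains the natural carrier of the effect when the data include baseline and the fixed part contains sales over time by condition.

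**Conclusion.** The point holds in conditional form. As written, the primary model names one random term that, read as an intercept, leaves the condition-by-time contrast with weekly residual error although 8 restaurants were randomized. The error rate can then be several times nominal: about 14-20% at τ/σ = 0.5 and 30-34% at 1.0 (pre/post coding, ordinary baseline, AR(1) 0 to 0.3). Serial correlation of 0.3 alone gives about 12-13%. It is about 5% with neither feature, and below nominal with all-zero baselines and little heterogeneity.

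This rests on an assumed two-sided 5% level, the random-intercept reading, condition-by-time as the tested term, residual-type df, and assumed values of τ/σ and serial correlation. The blanket claim that the primary standard errors and p-values are invalid goes beyond what the article shows.

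**What to change.** Make the restaurant the unit of inference for the primary contrast, in one of two ways.

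1. Analyse one summary per restaurant: mean weekly sales of new items over the intervention weeks, or change from baseline where the outcome has a baseline. Compare conditions on 6 df, or 3 df within pairs. Because the new items are not on the menu at baseline, any baseline covariate should be something measurable then, such as total or existing children's-menu sales. It costs one df (5, or 2 within pairs).
2. Keep the weekly model and add a restaurant-by-period random effect with between-restaurant df (for example Kenward-Roger), allowing for serial correlation if it can be estimated from eight restaurants.

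State the time coding, and report the estimate with a 95% CI on those df. The cost is a few sentences in the plan and, for the second option, a random-effect term, a df option and possibly a residual-covariance statement in SAS. Intervals will be wider, which reflects the true precision with 8 restaurants. The simulations tested the restaurant-level analysis, not the second option, so the first is the safer default.
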